#### Participant timeline

Patients meeting the inclusion criteria will be asked to participate during hospital admission. Potential participants will be given written and verbal information about the study and, if they agree to participate, will be asked to complete the informed consent document. The study coordinator will assign patients to the study groups using a previously-generated blinded random sequence. Participants will be contacted to specify the date of the baseline data collection visit. Sociodemographic and baseline characteristics will be evaluated at the beginning of the study. Follow-up evaluations will be made at 1, 3 and 6 months. Baseline and follow-up evaluations will be made by researchers unaware of the group to which each patient is assigned. Figure 2 shows the study flowchart and timeline.

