### Intervention group

CR with MI will be structured in four sessions, with an optional fifth session, in the six months after discharge. The methodology of the MI sessions will follow the four-phase logical sequence of MI proposed by Rollnick and Millner 1) engage in collaborative relationships, 2) focus on a particular change, 3) evoke intrinsic motivations for change, and 4) plan an immediate step for change [25]. MI will be administered by nurses trained through a certified MI course, who will be offered additional support and counseling. Collaborators will meet at least once a month to standardize the intervention and follow up of issues regarding MI. Each MI session will have defined contents and objectives to ensure homogeneity. The objectives of CR and secondary prevention will be introduced from the first session, (i.e., to increase participation in activities of daily living and self-care and follow recommendations on safe physical activity). Table 1 describes the MI program and the content of each session. Interviewers will collaborate in the coordination of care, ensuring continuity and communication between PHC family physicians, nurses, and the cardiologist).

**Table 1 Tab1:** Description of the intervention, content and aims of MI sessions

Session	Schedule and location	Duration	Aims	Content Description
#1	72 h Home	45 min	Relationship between patient and interviewer. Promote involvement of participant in CR	Presentation. General information on the program. Examine experiences, knowledge, motivation, self-confidence and expectations of CR and prevention
#2	2nd week PHC	20–30 min	Strengthen commitment and link with professional. Increase self-efficacy. Strengthen motivation	Identify specific objectives of patient to adjust to the CR plan. Collaborative work on personalized CR. Support and active listening to participant concerns. Examine participant resources
#3	5th week PHC	20–30 min	Maintenance therapeutic link. Empower participants. Increase self-efficacy. Strengthen motivation	Collaborative work. Support and active listening to patient concerns and adaptation of RC. Examine resources, barriers, and facilitators of patients. Manage discrepancies and resolving ambivalence. Discourse of maintenance

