			**Visit**													
**Activity/Task**	**Group**	**Agent, health care professional**	**v-**_**1**_	**v**_**0**_	**v**_**1**_	**v**_**2**_	**v**_**3**_	**v**_**4**_	**v**_**5**_	**v**_**6**_	**v**_**7**_	**v**_**8**_	**v**_**9**_^*****^	**v**_**9**_	**v**_**10**_	**v**_**11**_
Eligibility screen	Both	Research collaborator	x													
Informed consent	Both	Research collaborator	x													
Allocation	Both	Research collaborator		x												
Data collection of participant status	Both	Research collaborator			x			x				x			x	
Motivational interview	Intervention	Research collaborator			x		x		x		x		x			
Follow up: family physician	Both	Family physician				x			x					x		x
Follow up: PHC nurse	Both	PHC nurse				x			x					x		x
Six-minute walk test	Both	Research collaborator						x							x	
Follow up: cardiologist	Both	Cardiologist of the PHC area								x						
Blood analysis	Both	Research collaborator										x			x	

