### Limitations of the study

The study will be carried out in patients from a single, urban hospital. This may limit the generalizability of the results to semi-urban or rural areas. Second, the complete blinding of participants to their group assignment may not be guaranteed because patients may discover they have been assigned to the control group. However, this issue is common in MI research. Finally, the duration of the follow-up will not allow study of the long-term effects, although a subsequent study with a cohort design is possible. In addition, the proposed study is restricted to the improvement in the first six months of outpatient treatment of CR.

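### The self-report baseline is scheduled after allocation and at the same visit as the first motivational interview, so it can be affected by the session or by knowledge of the arm

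*Protocol article*

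**What the plan says.** The Participant timeline section of the protocol article sets out a sequence. Patients are approached and consent during admission. Then "The study coordinator will assign patients to the study groups using a previously-generated blinded random sequence". After that, "Participants will be contacted to specify the date of the baseline data collection visit". The same section says that baseline and follow-up assessors will not know the arm.

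Table 2 gives the same order by visit. Eligibility and consent are at v-1 and allocation is at v0. The row "Data collection of participant status" is first marked at v1, and the row "Motivational interview" is also first marked at v1.

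Table 1 describes that first session as a 45-minute home visit at 72 h. One of its aims is "Promote involvement of participant in CR", and its content is described as "Examine experiences, knowledge, motivation, self-confidence and expectations of CR and prevention". The Intervention group text adds: "The objectives of CR and secondary prevention will be introduced from the first session".

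The Limitations section accepts that "the complete blinding of participants to their group assignment may not be guaranteed".

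**The concern.** A baseline is useful because allocation cannot have influenced it. Here the first questionnaires come after allocation and share a visit with the first dose of the intervention. Table 4 lists PGWBI, SF-12, PAM-13 and HADS as self-administered, so an assessor who does not know the arm gives no protection: the patient produces the score.

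The session also works on what some of these scales measure. It deals with motivation and self-confidence, and PAM-13 is listed as a measure of activation and self-efficacy.

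Psychological wellbeing is part of the main objective, of secondary objective (iii) and of the hypothesis, and PGWBI and SF-12 are named secondary outcomes. If the intervention arm's first score is already raised, or the control arm's is lowered by disappointment, the two arms no longer start level. Any analysis that measures change from that value would then understate the benefit.

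**Working it through.** The plan gives no figure on this point, so there is none to reproduce. The check has three steps.

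**1. Order of events**

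| Step | Participant timeline section | Table 2 |
|---|---|---|
| Consent | during admission | v-1 (week 0) |
| Allocation | after consent | v0 (week 1) |
| First data collection | booked after assignment | v1 (week 1) |
| First motivational interview | not mentioned | v1 (week 1) |

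The two places agree that baseline follows allocation. Table 2 alone adds that baseline shares a visit with interview 1. Neither gives the order of tasks within v1. Table 2 names a research collaborator as the agent for both tasks. That label is generic and does not show that one person does both.

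**2. Which scales are involved**

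The Standard care group section counts questionnaires as part of data collection, identical in both arms. The Data management section times later questionnaires from a baseline one. No table lists scales by visit. PGWBI and SF-12 at v1 is a reasonable inference because they are named secondary outcomes. PAM-13 and HADS, listed among the other variables, are probable.

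**3. Which analyses would carry a disturbed baseline**

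Work in SD units, with equal variances at both times. Let D be the true between-arm effect at follow-up, s the baseline displacement (intervention minus control) caused by the session or by knowledge of the arm, and r the correlation between baseline and follow-up.

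- Follow-up values only: estimate = D.
- Change from baseline: estimate = D − s.
- Baseline-adjusted: estimate = D − r × s.

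The protocol gives none of D, s or r. The values below are assumptions, chosen only to show how the formulas behave, with D = 0.40:

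| s | Follow-up only | Change score | Adjusted, r = 0.5 | Adjusted, r = 0.7 |
|---|---|---|---|---|
| 0 | 0.40 | 0.40 | 0.40 | 0.40 |
| 0.1 | 0.40 | 0.30 | 0.35 | 0.33 |
| 0.2 | 0.40 | 0.20 | 0.30 | 0.26 |
| 0.3 | 0.40 | 0.10 | 0.25 | 0.19 |

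For example, at s = 0.2 and r = 0.5 the adjusted estimate is 0.40 − 0.5 × 0.2 = 0.30.

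Applied to the Statistical methods section:

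- The paired tests within each arm use the first value directly. A baseline raised by s in the intervention arm lowers that arm's change by s.
- The mixed model is affected if v1 is its first time point. The section does not say whether it is.
- The two-sample t-test between arms is unaffected if run on follow-up values.
- The six-minute walk test is marked in Table 2 only at v4 and v10, so the primary outcome has no v1 value to disturb.

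If s is negative, the same formulas overstate the benefit.

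**The case against.** The strongest reply is that contamination is not shown. A schedule table assigns tasks to visits and does not order them within a visit. That detail may sit in the full protocol or in the flowchart figure, which is not available here. This stands as far as it goes: a reader might infer that the questionnaires follow the interview, and the document does not say so. It does not remove the point, because the order that is stated already puts baseline after allocation and at the visit of an active session.

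A reader might also infer that patients are told their arm at v0. The Randomization section says that only the nurses giving the interviews know who is in that group. The Limitations section says only that patients may discover they are controls. Early disclosure is therefore possible but not documented.

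It is also fair to say that the protocol nowhere states that change from baseline is the response or that the baseline score is a covariate; the covariates it mentions are sociodemographic. The planned between-arm t-test may avoid the problem entirely. What remains exposed is the paired tests and, depending on its first time point, the mixed model.

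Finally, moving the scales into the admission is a trade-off. They would record the patient's state during an acute hospital stay, and within-arm changes would then include more of the natural recovery after discharge. That stands, and it is why the fix offers the ordering at v1 as well.

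**Conclusion.** The point holds as a weakness of the stated schedule. Both the timeline text and Table 2 place the baseline after allocation, and Table 2 places it with interview 1. The self-report baseline can therefore carry some effect of the session or of knowledge of the arm. The likeliest direction is an understated benefit: a session that raises scores and disappointment among controls both push that way. A reaction to the allocation could also run in the opposite direction.

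The size cannot be derived from the document. A reader might take a percentage loss from an assumed shift, but that would only restate the assumption. The table of estimates shows which analyses are sensitive, not how much bias to expect. The conclusion rests on two inferences: that the named secondary scales are among the data collected at v1, and that the paired tests or the mixed model use that value. The primary outcome and a between-arm comparison of follow-up scores are not affected. The change is still worth making, because it costs little and protects outcomes that appear in the trial's main objective.

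**What to change.** Amend Table 2 and the Participant timeline section so that, in both arms, the self-report baseline scales are completed before the arm is disclosed to the patient and before interview 1 starts. There are two ways to do it:

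- Keep the scales at v1 and state that the questionnaires come first, in both arms.
- Complete them after consent and before allocation, where the team accepts that the scores then reflect inpatient status.

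The cost is a change of wording and a slightly longer first contact. The sample size and the content of the intervention are not touched.

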**Fig. 2 Fig2:**
[figure not shown]
Study flowchart

### Sample size calculation

The six-minute walk test is sensitive and specific in measuring changes in functional capacity. Evidence shows the minimum clinically-relevant difference is 30 m [31, 32]. Accepting an alpha risk of 0.05 and a beta risk of 0.2 in a bilateral contrast, with a standard deviation of 80 m in the six-minute walk test, 284 participants (142 in the intervention group and 142 in the control group) will be required to detect differences of ≥ 30 m. To achieve adequate participant enrollment and reach the minimum sample size, we analyzed the incidence of new AMI in the six PHC areas and foresee that three years will be sufficient to reach the minimum sample size.

### Randomization

A randomization sequence will be generated and participants will be assigned using a centralized method with hidden assignation. Only the nurses who carry out the MI will be aware of the participants in the MI group. The assessments at 1, 3 and 6 months will be made by an assessor blinded to the group assignment. The study coordinator will record whether they were informed of the assignment of participants.

### Data management and monitoring

All study information will be saved securely, and all participant information will be stored using an electronic secure server system with limited access. The information will be identified by a coded identification number to ensure confidentiality. All records with names or other personal identifiers (like locator forms and informed consent forms) will be stored separately from study registers and identified by a coded number. The main database will be protected with a password-protected system.

Questionnaires will be stored after informed consent. Follow-up questionnaires will be collected at 3 and 6 months after the baseline questionnaire. For follow-up visits (control blood tests and administration of questionnaires), a researcher will make an appointment with patients by phone and provide the dates of interviews.

Data management and monitoring will follow the pre-planning foreseen in the monitoring plan. A data monitoring committee (principal investigator, statistician and a collaborator from each PHC) will ensure the integrity of data recording.

### Statistical methods

Outcomes will be evaluated at 1, 3 and 6 months. Participant characteristics will be described using central tendency measures: mean or median and variability: standard deviation or interquartile range for continuous variables, and frequencies and percentages for categorical variables. The results of the physical functional capacity and the six-minute walk test will be transformed into units of metabolic equivalent of task (MET) using the equation and conversion table of the American College of Sports Medicine [33]. Between-group differences will be studied using the Student’s t-test for two samples. The magnitude of the effect will be calculated using Cohen's D. The effect of the intervention or standard care will be calculated using the Student’s t-test or Mcnemar’s test for paired samples. A mixed linear regression model will be used to evaluate trends in each arm, adjusting for variables of interest. For the inference analysis, co-variables that correlate (sociodemographic factors) will be used and adjusted analyzes made. In the comparison of multiple hypotheses, adjustment of the level of statistical significance (α = 0.05) will be used to avoid type I errors. All analyzes will made per protocol and intention-to-treat. The analysis will be made using R v3.5.2 [34].

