### Secondary objectives and hypothesis

(i) To compare improvements in functional capacity and changes in risk factors (secondary prevention). (ii) To evaluate the impact of the CR program according to adherence to therapy (drug treatment and physical activity program) and health service use and (iii) to evaluate the efficacy of the CR program based on psychological factors and quality of life after AMI.

The hypothesis of the study is that a PHC CR program with MI after AMI has a positive impact on functional and psychological wellbeing and quality of life compared to standard care.

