#### Psychological status and quality of life

Measured by the Psychological General Well-Being Index (PGWBI) [29] and the generic SF-12 [30].

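### The stated two-sample t-test for PGWBI and SF-12 is valid, but less precise than a comparison adjusted for the baseline score, and the plan commits to no such adjustment.

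*Protocol article*

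**What the plan says.** Under Statistical methods, the only method named for comparing the arms is this: "Between-group differences will be studied using the Student’s t-test for two samples". Whether it is applied to follow-up values or to changes is not stated. Three other sentences in that section bear on the point:

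- Paired tests: "The effect of the intervention or standard care will be calculated using the Student’s t-test or Mcnemar’s test for paired samples".
- Mixed model: "A mixed linear regression model will be used to evaluate trends in each arm, adjusting for variables of interest".
- Covariates: "For the inference analysis, co-variables that correlate (sociodemographic factors) will be used and adjusted analyzes made".

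The PGWBI and SF-12 are listed under Secondary outcomes as the measures of psychological status and quality of life. Data management and monitoring says: "Follow-up questionnaires will be collected at 3 and 6 months after the baseline questionnaire". Participant timeline also plans a baseline evaluation, and Table 2 has data collection at v1 in both arms. No section lists the instruments by visit.

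Psychological wellbeing is part of the main objective. The hypothesis is that the programme "has a positive impact on functional and psychological wellbeing and quality of life compared to standard care".

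**The concern.** A patient's score before treatment usually predicts the score afterwards. If that baseline score is collected but not used well, the between-arm interval is wider than it need be.

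The two readings of the t-test fail differently. On follow-up scores, any chance difference between arms at baseline passes into the estimate, multiplied by the baseline to follow-up correlation. On change scores the baseline is used, but with a fixed weight of one instead of the weight that the data support.

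At stake is the precision of the wellbeing and quality-of-life results. They are secondary outcomes, but they carry part of the study hypothesis, and the sample size was set on the walk test alone.

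**Working it through.** **Inputs from the article (Sample size calculation).** 142 per arm; two-sided alpha 0.05; power 80%; walk-test difference 30 m and SD 80 m. No effect size, SD, power or correlation is given for the PGWBI or SF-12.

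**The article's own figure.** It concerns the walk test only. With d = 30/80 = 0.375, a two-sample t-test at 80% power needs 112.6, so 113 per arm or 226 in all. The stated 284 is larger. It would follow from an unstated 20% loss, since 113/0.8 = 141.25, rounded up to 142. That is a separate matter, but it makes 113 a reasonable lower value for the number analysed per arm.

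**Assumptions.** A standardised difference of d = 0.30 SD, and a baseline to follow-up correlation r of 0.4 to 0.6, with equal SDs at both times.

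**Variance of the arm difference, relative to a t-test on follow-up scores.**

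- Follow-up scores: 1
- Change scores: 2(1 − r)
- ANCOVA: 1 − r²

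ANCOVA is more precise than follow-up scores whenever r is not zero. Against change scores the variance ratio is 2(1 − r)/(1 − r²) = 2/(1 + r), which exceeds 1 for every r below 1. Change scores are worse than follow-up scores when r is below 0.5.

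**Power.** The effective difference is d for follow-up scores, d/√(2(1 − r)) for change scores and d/√(1 − r²) for ANCOVA, each put into the noncentral t distribution. At r = 0.5, for example, ANCOVA has 0.30/√0.75 = 0.346. With 142 analysed per arm:

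| r | t-test, follow-up | t-test, change | ANCOVA |
|---|---|---|---|
| 0.4 | 71.2% | 63.3% | 78.5% |
| 0.5 | 71.2% | 71.2% | 82.9% |
| 0.6 | 71.2% | 80.4% | 88.3% |

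With 113 analysed per arm and r = 0.5, power is 61.2% for either t-test and 73.7% for ANCOVA.

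**Equivalent sample size.** At r = 0.5 the variance falls by 25%. A t-test on follow-up scores would need 284/0.75 = 379 patients to match ANCOVA on 284.

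**Chance imbalance.** With 142 per arm, the baseline difference between arms has a standard error of √(2/142) = 0.119 SD, so its 95% range is ±0.233 SD. On follow-up scores it moves the estimate by r times that amount, up to 0.5 × 0.233 = 0.12 SD at r = 0.5. That is sizeable beside an effect of 0.30 SD.

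**Do the other planned analyses already cover this?**

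- The paired tests use the baseline, but within each arm, so they give no estimate of the difference between arms.
- The mixed model is described as examining the course within each arm. No between-arm contrast is stated, and its adjustment variables are not named.
- The adjusted analyses name sociodemographic factors only.

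None of the three commits to a between-arm contrast adjusted for the baseline score.

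**The case against.** The strongest case on the other side has four parts.

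1. **The t-test is valid.** Under randomisation it is unbiased on average and keeps its type I error, and its standard error already allows for chance imbalance. This stands. The point is one of precision, and of the estimate in the trial actually drawn.
2. **The baseline may already be used.** A reader might infer that the plan throws the baseline score away. The article does not support that: the test may be on changes, and the unnamed covariates of the mixed model could include the baseline score. What remains is that change scores are still less precise than ANCOVA, and that nothing in the text commits to the adjustment.
3. **A condensed article leaves model terms to the full plan.** That is fair for covariate lists. Here, though, the article does fix a between-arm method, and a better one is available from data that it already plans to collect.
4. **The size is assumed.** This stands. Effect size and correlation are not in the document. Alpha of 0.05 ignores the multiplicity adjustment that the article plans, and 142 analysed per arm allows for no loss. The gain also depends on the comparator: at r = 0.6 it is from 71.2% to 88.3% against follow-up scores, but only from 80.4% to 88.3% against change scores.

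A reader might also extend the point to the primary outcome. The documents do not allow this: Table 2 schedules the six-minute walk test only at weeks 4 and 23, so there is no baseline walk distance to adjust for.

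**Conclusion.** The point holds as a matter of efficiency on secondary outcomes. Over the assumed correlations of 0.4 to 0.6, ANCOVA is more precise than the t-test under both readings. At 0.30 SD and 142 analysed per arm, it adds 7.3, 11.7 or 17.1 percentage points of power over follow-up scores, and 15.2, 11.7 or 7.9 points over change scores, at r = 0.4, 0.5 and 0.6.

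These gains rest on the assumed effect and correlations, on the inference that the baseline questionnaire includes the PGWBI and SF-12, and on an unadjusted alpha of 0.05. The direction does not depend on the particular effect size or correlation chosen. A reader might infer that the planned wellbeing results would be invalid or biased by design; they would not be. The change is worth making because it gains precision at almost no cost.

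**What to change.** For the PGWBI and the SF-12 physical and mental summaries, replace the two-sample t-test as the between-arm analysis with one of these:

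- an ANCOVA of the 6-month score, with arm and the patient's own baseline score; or
- the planned mixed model, with the follow-up scores as outcomes and baseline score, arm, visit and arm-by-visit as terms, over the follow-up visits at which the scales are collected.

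Report the adjusted arm difference at 6 months with its 95% confidence interval.

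Table 2 places v1 data collection after allocation (v0) and at the same visit as the first motivational interview. State that the baseline questionnaires are completed before that interview starts, so that the session cannot affect the covariate.

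The cost is a change of wording in Statistical methods, one degree of freedom for the covariate, a stated rule such as simple imputation for a missing baseline score, and a small change in the order of tasks at v1. No visit, staff or instrument is added.

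### The plan calls within-arm paired tests the effect of the intervention, although only the between-arm contrast can measure it

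*Protocol article*

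**What the plan says.** The hypothesis is comparative. Under Secondary objectives and hypothesis, the programme is expected to show that it "has a positive impact on functional and psychological wellbeing and quality of life compared to standard care". The sample size is a two-group calculation for the six-minute walk test.

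The Statistical methods section first gives a two-sample t-test for differences between groups, with Cohen's d for the size of the effect. It then states: "The effect of the intervention or standard care will be calculated using the Student’s t-test or Mcnemar’s test for paired samples". The next sentence reads: "A mixed linear regression model will be used to evaluate trends in each arm, adjusting for variables of interest". The section does not say which of these analyses decides the main outcome.

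For categorical outcomes, McNemar's paired test is the only test named. The secondary-prevention outcome groups five targets (blood pressure, LDL cholesterol, HbA1c, smoking and body mass index). Each is a threshold or a yes/no state.

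The schedule in Table 2 marks the walk test at week 4 and week 23 only. Table 1 places motivational session 1 at 72 hours and session 2 in week 2.

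**The concern.** A before-after test within one arm answers whether patients in that arm changed. The trial asks whether patients offered the programme end up better than those who were not. The two questions differ by whatever change the arms have in common, and here some common change is likely. Controls receive the information kit and the home exercise programme, and both arms see the family physician, the nurse and the cardiologist.

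If the sentence is followed literally, a significant gain in the intervention arm would be reported as the programme's effect even when controls gained just as much. The same holds for a table with one p-value per arm. For binary outcomes the risk is greater, because the plan names no between-arm test beside McNemar's.

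**Working it through.** **1. The contrast the trial is sized on.** Inputs from Sample size calculation: a two-sided alpha of 0.05, power of 80% (beta 0.2) and an SD of 80 m. On the difference to detect, the section says: "Evidence shows the minimum clinically-relevant difference is 30 m". Its result is given as: "284 participants (142 in the intervention group and 142 in the control group) will be required".

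n per arm = 2 × (1.96 + 0.842)² × (80/30)² = 2 × 7.85 × 7.11 ≈ 112; the exact t calculation gives 113. The stated inputs therefore give 224 to 226 in total, not 284. A 20% loss, which the article does not state, would give 113/0.8 = 141.25, so 142 per arm and 284 in total. Either way this is a two-sample calculation, and the figure is not disputed here. With 142 per arm, a true 30 m difference is detected by the two-sample test with power of about 88%: 30/(80 × √(2/142)) = 30/9.49 = 3.16, and Φ(3.16 − 1.96) = Φ(1.20) ≈ 0.88.

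**2. What each test estimates.** Let both arms gain r metres between the two tests and let the programme add δ.
- Paired test, intervention arm: expected change r + δ.
- Paired test, control arm: expected change r.
- Between-arm contrast: (r + δ) − r = δ.

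Only the last is free of r.

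**3. Size when δ = 0.** The article gives neither the shared gain nor the correlation between repeated walk tests, so both are assumptions. With SD 80 m at each test and correlation ρ, the SD of change is 80 × √(2(1 − ρ)): 80 m at ρ = 0.5 and 62 m at ρ = 0.7. For n = 142:

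P(paired test significant) ≈ Φ(r / (SD/√142) − 1.96)

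- r = 20, SD 80: 20/6.71 = 2.98; Φ(1.02) ≈ 0.85.
- r = 20, SD 62: 20/5.20 = 3.84; Φ(1.88) ≈ 0.97.

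The noncentral t distribution gives nearly the same values:

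| Assumed shared gain | Paired test significant, SD 80 m | Paired test significant, SD 62 m |
|---|---|---|
| 10 m | 32% | 48% |
| 20 m | 84% | 97% |
| 30 m | 99% | 100% |

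In 5,000 simulated null trials per scenario (SD of change 62 m), the two-sample test was significant in about 4-6% at every gain tried, from 0 to 30 m.

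**4. The pair available for the walk test.** The first scheduled test, at week 4, comes after allocation and after sessions 1 and 2. A paired walk-test result is then change from a point already inside the intervention. It includes shared recovery after week 4 and leaves out anything the programme achieved before week 4.

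**5. Binary outcomes.** McNemar's test compares a patient's status at two times within one arm. Step 2 applies unchanged: if both arms move towards target equally, the test can be significant in each with no programme effect.

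**The case against.** The strongest reply is that a randomised comparison is planned and comes first. The two-sample t-test and Cohen's d precede the disputed sentence, the hypothesis is comparative, and the trial is sized on the between-arm difference. The sentence also speaks of an effect of standard care, so it may loosely mean change within each arm. This stands in part. For the walk test and other continuous outcomes a valid between-arm test exists, and the plan nowhere says that the paired tests decide the trial. It does not remove the problem: the plan attaches the word effect to a test that cannot estimate one, and does not rank the analyses.

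A reader might infer more than the article supports:
- **That the trial will credit natural recovery to the programme.** That would follow only if the paired results are reported as the effect. The planned two-sample test is not affected by shared recovery.
- **That the mixed model leaves out an arm-by-visit term.** The text says only what the model will be used for. A single model with that term would also yield trends in each arm.
- **That the composite will have no randomised test.** The article does not say that the composite is binary. A count of targets met could go through the two-sample t-test.
- **That significance in one arm only would be common.** With p the chance in each arm, the pattern of intervention significant and control not has probability p(1 − p). This is 22-25% at a 10 m gain (0.32 × 0.68 and 0.48 × 0.52), but about 13% or 3% at 20 m (0.85 × 0.15 and 0.97 × 0.03).
- **That the covariates are chosen from the data.** The wording "co-variables that correlate (sociodemographic factors) will be used and adjusted analyzes made" is vague but limits the pool. It is a matter of detail and forms no part of this point.

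**Conclusion.** The point holds as a fault in a stated rule. As written, the effect of the intervention is to be calculated by a method that measures change over time, and the only categorical test named is of the same kind. The planned two-sample comparison of the walk test is sound and is not in question.

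If the paired result in the intervention arm were read as the effect, a programme that adds nothing would appear effective in roughly 85-97% of trials instead of about 5%. This assumes a shared gain of 20 m, a change SD of 62 to 80 m, and complete data on 142 per arm. With 113 per arm the range is 75-93%. A smaller shared gain lowers the figure (32-48% at 10 m with 142 per arm), and with no shared gain the paired test returns to about 5%. The direction of the error does not depend on these assumptions, but its size does.

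The point applies most to outcomes analysed as binary: the individual secondary-prevention targets, and the composite if it is handled that way.

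**What to change.** Amend the Statistical methods section to say the following:

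1. The effect of the programme is the between-arm contrast.
2. For continuous outcomes, fit one mixed model to all participants with arm, visit and arm-by-visit, and report the between-arm difference at the 6-month visit (week 23) with a 95% confidence interval. For the walk test, report that difference itself and not the interaction alone, because week 4 is not a pre-intervention baseline.
3. For binary outcomes, use a between-arm logistic or risk-difference model at the same visit.
4. Paired t and McNemar results describe change within each arm and carry no claim of effect.

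The cost is a change of wording and a little extra analysis code. The data to be collected, the sample size and the software stay as they are.
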